#### Covariates

##### Inventory of Interpersonal Problems (IIP-32; 47)

The IIP-32 measures difficulties people experience in their interpersonal relationships. For example, things people find ‘too hard’ or do ‘too much’. The IIP-32 taps into 8 domains which includes hard to be assertive, hard to be sociable, hard to be supportive, too dependent, too caring, too aggressive, hard to be involved, and too open. Respondents answer each item using a scale ranging from 0 (not at all) to 4 (extremely). Internal consistencies for each domain have been shown to be acceptable: assertive: *α* = .86, sociable: *α* = .89, supportive: *α* = .75, dependent: *α* = .71, caring: *α* = .72, aggressive: *α* = .85, involved: *α* = .75, and open: *α* = .80. Overall, the internal consistency for the IIP-32 is good .86 [46].

##### COVID-19 impact

The impact of COVID-19 on the participant in the prior 7 days will be assessed using a single-item measure. The item is measured on a 5-point Likert scale from 1 (not at all affected) to 5 (greatly affected).

#### Exploratory

##### Usability

Consistent with previous trials of +Connect, usability will be assessed post-intervention using an 8-item satisfaction rating scale. Each item ranges from 1 (extremely disagree) to 5 (extremely agree). Items relate to the format, font, colour scheme, and how easy the application was to navigate and use.

### Participant timeline {13}

The participant timeline is as follows:Screening: a brief phone call or face-to-face assessment to verify initial inclusion and exclusion criteria.The baseline assessment and secondary verification procedure will be conducted 1–7 days after screening.If eligible, participants will be randomised to either Peer Tree or control.Peer Tree participants will wait until a suitable number of participants is available to be onboarded onto the Peer Tree application. This will be dictated by recruitment speed. Once enough participants have been randomised to Peer Tree, the intervention will begin. After 6–8 weeks, participants will be seen for the post-intervention assessment.Control participants will wait for 6 weeks before starting the post-intervention assessment.Three months following the completion of the post-intervention assessment, participants will complete the third and final assessment. Once the follow-up assessment is complete, the study is completed.

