## Methods

### Trial design {8}

Peer Tree is a pilot randomised controlled trial utilising a parallel groups design where participants are randomly allocated to either the Peer Tree intervention or control (i.e. No Peer Tree) group. There will be no blinding in this trial for assessors. Once determined to be eligible during the baseline assessment, participants will be randomised to one of the two conditions. Participants in both groups will complete a post-intervention assessment 6 weeks after the baseline or once they have finished the intervention. Participants in the Peer Tree arm will be given a maximum of 8 weeks to complete the smartphone application, after which they will complete the post-intervention assessment. Participants will then complete a follow-up assessment 3 months after the post-intervention assessment. Figure 1 displays the Consolidated Standards of Reporting Trials (CONSORT) flow diagram of the study procedure. The protocol was designed in accordance with the Standard Protocol Items: Recommendations for Interventional Trials (SPIRIT) and Good Clinical Practice Guidelines.

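### Only the Peer Tree arm has an uncapped onboarding wait after baseline, so it is assessed later than control and the loneliness comparison spans unequal elapsed time

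*Protocol article*

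**What the plan says.** Participant timeline {13} of the protocol article gives the order of events: screening, baseline, randomisation. The arms then diverge.

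- **Peer Tree:** "Peer Tree participants will wait until a suitable number of participants is available to be onboarded onto the Peer Tree application". On the length of that wait the section says only "This will be dictated by recruitment speed". Then: "Once enough participants have been randomised to Peer Tree, the intervention will begin". Then: "After 6–8 weeks, participants will be seen for the post-intervention assessment".
- **Control:** "Control participants will wait for 6 weeks before starting the post-intervention assessment". No onboarding wait is mentioned for this arm.
- **Follow-up, both arms:** "Three months following the completion of the post-intervention assessment, participants will complete the third and final assessment".

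Trial design {8} describes the same visit in other terms: "Participants in both groups will complete a post-intervention assessment 6 weeks after the baseline or once they have finished the intervention". It adds: "Participants in the Peer Tree arm will be given a maximum of 8 weeks to complete the smartphone application". It does not mention the onboarding wait.

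Statistical methods {20a} enters time as a repeated factor with three levels (baseline, post-intervention, follow-up) and group as the between-participant factor. Nothing in the article provides a repeat baseline when the app starts, a control visit matched to a batch, or elapsed time in the model.

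**The concern.** The wait begins after randomisation and exists in one arm only, so randomisation does not balance it. The analysis asks whether loneliness changes more in one group between nominal visits. If those visits lie further apart in one group, anything that moves loneliness over weeks without the app enters the group comparison.

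The article itself gives reasons to expect such movement. Its background ties loneliness in students to the transition to university and the forming of new peer groups. It measures COVID-19 impact at every visit, and Trial status places the work in 2020–2021.

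There are two further consequences. The Peer Tree baseline ages while participants wait, and dropout during that wait can occur in that arm only. Because the Peer Tree visit may also be triggered by finishing the app, its timing depends partly on adherence.

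Loneliness is the outcome at stake. It is the first-named primary outcome in Outcomes {12}, the subject of the main hypothesis in Objectives {7} and the basis of the sample size.

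**Working it through.** The plan states no figure for the wait or the gap, so there is none to reproduce. The sample size of 42 does not enter the timing result.

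**Inputs**

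- Onboarding wait in Peer Tree: w weeks, with no value or maximum given (Participant timeline {13}).
- App start to post-intervention visit: 6 to 8 weeks (Participant timeline {13}; the 8-week maximum is also in Trial design {8}).
- Control post-intervention visit: 6 weeks (Participant timeline {13}), counted from baseline (Trial design {8}).
- Follow-up: 3 months after the participant's own post-intervention visit, taken here as 13 weeks.

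**Formulas, in weeks from baseline**

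- Control: post-intervention = 6; follow-up = 6 + 13 = 19.
- Peer Tree: post-intervention = w + 6 to w + 8; follow-up = w + 19 to w + 21.
- Gap at both visits = (w + 6 to w + 8) − 6 = w to w + 2.

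| Wait w | Peer Tree post-intervention | Control | Gap | Peer Tree follow-up | Control |
|---|---|---|---|---|---|
| 0 | 6–8 | 6 | 0–2 | 19–21 | 19 |
| 2 | 8–10 | 6 | 2–4 | 21–23 | 19 |
| 4 | 10–12 | 6 | 4–6 | 23–25 | 19 |
| 8 | 14–16 | 6 | 8–10 | 27–29 | 19 |

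The clocks coincide only if the wait is zero and the visit falls at exactly 6 weeks.

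**How long might the wait be?** Batch size and recruitment period are not in the article, so this is illustration only. Assume 21 Peer Tree participants (half of 42) arriving evenly over T weeks, so r = 21/T per week, in batches of b. Mean wait = (b − 1)/(2r); longest wait = (b − 1)/r.

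- b = 5, T = 26: mean 2.5 weeks, longest 5.0.
- b = 5, T = 52: mean 5.0, longest 9.9.
- b = 10, T = 52: mean 11.1, longest 22.3.

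**The adherence part.** A new module opens each day, and only if the previous one is complete. The 42 modules therefore take about 42/7 = 6 weeks at best. With the 8-week limit, finishing speed can move the visit by about 8 − 6 = 2 weeks. The rest of the gap comes from the wait.

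**What this means for bias.** Roughly, bias = drift per week × mean gap. The documents give neither. If drift were 0.01 to 0.05 SD per week and the mean gap 2 to 10 weeks (both assumed), the product runs from 0.01 × 2 = 0.02 SD to 0.05 × 10 = 0.50 SD, with either sign. A range that wide shows the size is unknown; it is not an estimate.

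**The case against.** **The two sections need not contradict each other.** The sentence in Trial design {8} can be read as assigning six weeks to controls and completion to Peer Tree. That fits Participant timeline {13}, with the wait merely left out. This is a fair reading, and a flat contradiction should not be claimed. It still leaves the arms on different clocks.

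**Controls may have been meant to count from onboarding.** Participant timeline {13} does not say when their six weeks begin; only Trial design {8} names baseline. If batch start was intended, the gap falls to 0–2 weeks. No section says so.

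**There is partial protection.** Block randomisation at 1:1 makes the arms concurrent, staggered entry spreads baselines over the calendar, and the COVID-19 item is listed as a covariate and collected at all three visits. These soften calendar effects. They do not equalise time since baseline.

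**It is a pilot.** Acceptability, feasibility and safety, three of the four primary outcomes in Outcomes {12}, do not rest on between-arm change at matched times. That lowers the severity. Loneliness does rest on it.

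**Stronger readings the documents do not support.** A reader might infer a bias that is large against the planned effect, or one that favours Peer Tree. Sample size {14} says only that the effect is moderate, without a number, and the sign of any drift is unknown. A shift worked out for the participant with the longest lag would also overstate the matter, because the arm comparison depends on the mean gap. A reader might also invoke regression to the mean, but Eligibility criteria {10} sets no loneliness threshold, so that mechanism is weakly supported.

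**Conclusion.** The point holds as a defect of the visit schedule. By plan, Peer Tree is assessed w to w + 2 weeks later than control at post-intervention and again at follow-up, with w uncapped. The nominal-visit analysis therefore compares change in loneliness over unequal elapsed time. This rests on the controls' six weeks starting at baseline, as Trial design {8} states.

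Confidence is high on the asymmetry and low on its effect: the documents allow neither a size nor a direction for the bias. It would be wrong to conclude that the loneliness result must be seriously distorted. It would be equally wrong to conclude that modelling actual time afterwards would put it right. Controls are all planned at week 6 and Peer Tree at or after it, so arm and elapsed time barely overlap.

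Severity: should-fix.

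**What to change.** 1. **One clock for participants not yet assessed.** Give each control the start date of the Peer Tree batch recruited in the same period. Hold the post-intervention assessment at the same fixed number of weeks after that date in both arms, for example the plan's own 8-week maximum, whether or not the app is finished. Set follow-up from the same date. With an 8-week visit, both arms are assessed at w + 8 weeks from baseline, the planned gap is zero at both visits, and visit timing no longer depends on adherence.
2. **Reconcile Trial design {8} and Participant timeline {13}** on when the interval to the visit starts, how long it is, and the onboarding wait.
3. **For those already assessed,** report days from baseline to each visit by arm. A model using actual time may be shown as a sensitivity analysis, with the stated limitation that it cannot fully separate arm from elapsed time.

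Holding randomisation until a batch is ready would also remove the wait-driven gap. However, it conflicts with giving the allocation during the baseline session (Implementation {16c}) and would age the baseline in both arms.

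**Cost.** Rescheduling and wording only, with no new visits or staff. With an 8-week visit, controls wait w + 2 weeks longer than now. Participants who finish in 6 weeks are measured up to about two weeks after completing the app, which slightly changes what post-intervention means for them. Trial status says data collection is under way, so the change helps only visits still to come.

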### Sample size {14}

A power analysis was conducted using G*Power 2.0 software. The *F* statistic function for an intervention design was used to obtain the relevant sample size. This is established using loneliness outcome data and is estimated using the effects sizes derived from +Connect. Loneliness was used to determine statistical power as it was the target variable of our primary outcomes. This revealed that 42 participants are needed to detect a moderate effect with 80% power.

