**Methods:**

This will be a pilot randomised controlled trial (RCT) comparing a strength-based digital smartphone application (Peer Tree) with a control condition. Forty-two young people enrolled at university will be recruited for this pilot RCT. Participants with suicidal ideation or behaviours, acute psychiatric symptoms in the past month, or a current diagnosis of a mood or social anxiety disorder will be excluded. Allocation will be made on a 1:1 ratio and will occur after the initial baseline assessment. Assessments are completed at baseline, at post-intervention, and at follow-up. Participants in the control condition complete the same three assessment sessions. The primary outcome of the study will be loneliness. Depression, social anxiety, quality of life, acceptability, usability, feasibility, and safety of Peer Tree will also be measured as secondary outcomes.

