## Objectives {7}

The objective of this study is to evaluate the acceptability, feasibility, safety, and initial efficacy of a positive psychology smartphone application intervention called Peer Tree. Peer Tree is a digital smartphone intervention targeting loneliness and is a new iteration of our previous application +Connect. Peer Tree includes many features from +Connect [30, 31] but also includes the personalisation of modules based on user symptom profiles, a peer- and clinician-moderated chat forum, and animated videos to address loneliness in young people using a positive psychology framework.

It is hypothesised that Peer Tree participants, compared with the control participants, will report significantly lower loneliness at post-intervention, and these effects will remain at follow-up. It is also anticipated that Peer Tree participants, compared with control participants, will report significantly lower social anxiety and depressive symptoms, and higher quality of life and well-being outcomes at post-intervention as well as at follow-up.

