##### Peer tree feasibility

Feasibility will be assessed by considering four key factors: uptake, attrition, retention, and application completion. Uptake is defined as the number of potentially eligible young people who attended the baseline assessment. We set an apriori threshold of at least 50% of people who were eligible would attend a baseline assessment. Attrition is defined as the number of participants who attended the baseline assessment but failed to log into the app for more than three consecutive days and where researchers were unable to contact the participant. We set a priori threshold of a 30% attrition rate. Retention is defined as the number of participants who complete the intervention. Application completion is defined as accessing and completing at least 50% of the app (21 out of 42 days) within the maximum allocated time of 8 weeks. These criteria are consistent with our previous pilot trials of +Connect [32, 33].

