## Statistical methods

### Statistical methods for primary and secondary outcomes {20a}

All data processing and analysis will occur either in the statistical package for the Social Sciences (SPSS) or Mplus. Data manipulation will only occur if the data violates the statistical assumptions for the tests that we would be conducting. In this instance, the data will be transformed into a format that does not jeopardise the interpretability of the scores.

An intention-to-treat (ITT) analysis will also be conducted on all participants who were enrolled in the project but dropped out of the study. A mixed-model analysis will be used to determine whether a greater change in loneliness occurs over time for the Peer Tree group compared with the control group. This form of analysis creates an unbiased view of the intervention by including every participant who was assigned to each group in the final analysis, rather than those who contributed to each data point in the study. That is, if 15 people were assigned to an intervention but only nine of them completed the intervention, the ITT analysis would include all 15 participants in the analysis to provide an appropriate measure of what the effect would look like with every participant included.

A per-protocol analysis using mixed-model analysis of variance will be conducted to determine whether a change in loneliness occurs over time more so for the Peer Tree group compared with the control condition. Time (i.e. baseline, post-intervention, follow-up) will be the repeated measure factor, while intervention (i.e. Peer Tree vs control) will be the between-participant factor. Two-tailed Pearson’s *r* correlations will be calculated to assess the relationships between our primary outcome, loneliness, and secondary outcomes. This will be used to determine the suitability of conducting additional, regression-based analyses. In the instances that there are violations to the assumptions of these tests, we envisage that any combination of the following will be used to answer our focal questions: standard and hierarchical regression, mediation and multiple mediation, latent trajectory modelling, *t*-tests, and mean comparisons.

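### The 80% power claimed for a moderate effect with 42 participants fits a between-arm difference of about 0.85 SD; 0.5 SD has roughly 35–75% power, and no loss is allowed for

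*Protocol article*

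**What the plan says.** All references are to the protocol article.

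- **Sample size {14}:** the calculation was done in G\*Power. "The *F* statistic function for an intervention design was used to obtain the relevant sample size", and the target "is estimated using the effects sizes derived from +Connect", the team's earlier app. The result is given as: "This revealed that 42 participants are needed to detect a moderate effect with 80% power".
- **Abstract, Methods:** "Forty-two young people enrolled at university will be recruited for this pilot RCT", allocated 1:1, so 21 per arm.
- **Objectives {7}:** compared with controls, Peer Tree participants "will report significantly lower loneliness at post-intervention, and these effects will remain at follow-up".
- **Statistical methods {20a}:** a mixed model compares change in loneliness between groups. In the per-protocol version, "Time (i.e. baseline, post-intervention, follow-up) will be the repeated measure factor" and arm is the between-participant factor.
- **Peer tree feasibility:** "We set a priori threshold of a 30% attrition rate". Attrition there means a lapse in app log-ins of more than three consecutive days, combined with failure to reach the participant.
- **Section {20c}:** data missing because of withdrawal are not imputed.

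**The concern.** The power sentence and the hypothesis are on different scales. A reader of the sample size section will take moderate to describe the difference in loneliness between the arms, because that is what the objectives predict. An interaction effect size f is a different quantity: a value that looks small or medium as f can be a large difference between arms. If that happened here, the trial has much less power for a moderate benefit than the sentence implies.

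Two consequences follow. A non-significant loneliness result could be read as evidence against a moderate benefit that the trial would often have missed. A later trial could also copy 42 as a validated sample size. In addition, the number needed equals the number recruited, so any lost outcome takes the trial below its own target.

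**Working it through.** **Inputs.** From the article: N = 42, 1:1 allocation, three occasions, 80% power, an F test, 30% attrition threshold. Assumed because not given: two-sided alpha 0.05; correlation ρ between occasions of 0.5 to 0.8; moderate = 0.5 SD between arms.

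**1. Reproducing 42.** For a group-by-time interaction with m occasions, λ = f²·N·m/(1 − ρ), with df (m − 1) and (N − 2)(m − 1). With f = 0.20, m = 3, ρ = 0.5: λ = 0.04 × 42 × 3/0.5 = 10.08 on 2 and 80 df, power 80.3%. N = 40 gives 78.2%, so 42 is the smallest even number reaching 80%. The solution is not unique: f = 0.25 with ρ = 0.22 also gives 42.

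**2. Converting f to a between-arm difference.** Let the arms differ by 0, δ, δ at the three visits. Deviations from the mean difference are −2δ/3, δ/3, δ/3, and each arm carries half of these. Then f² = (1/3) × (1/4) × (6/9)δ² = δ²/18, so δ = 4.243·f.

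- f = 0.20 gives 0.85 SD.
- f = 0.25 gives 1.06 SD.
- Conversely, δ = 0.5 SD gives f = 0.118.

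**3. Power for 0.5 SD with 21 per arm.**

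- Unadjusted two-sample t: noncentrality 0.5/√(2/21) = 1.62 on 40 df, power 35%. Reaching 80% needs 64 per arm.
- Three-occasion interaction: λ = (0.25/18) × 42 × 3/(1 − ρ) = 1.75/(1 − ρ).
- Baseline-adjusted: standardised difference 0.5/√(1 − ρ²) on 39 df.

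| ρ | Interaction λ | Interaction power | Adjusted difference | Adjusted power |
|---|---|---|---|---|
| 0.5 | 3.50 | 36% | 0.577 | 45% |
| 0.7 | 5.83 | 55% | 0.700 | 60% |
| 0.8 | 8.75 | 74% | 0.833 | 75% |

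**4. Difference detectable with 80% power at 21 per arm.** Unadjusted, 0.89 SD. Baseline-adjusted, 0.886 × √(1 − ρ²): 0.77 SD at ρ = 0.5 and 0.63 SD at ρ = 0.7.

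**5. Effect of loss, if 30% of outcomes went missing.** 42 × 0.7 = 29.4. With f = 0.20 and ρ = 0.5, 30 completers give λ = 7.20 and 64% power; 29 give λ = 6.96 and 63%. For 0.5 SD (21 × 0.7 = 14.7, taken as 15):

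| Completers | Unadjusted | Adjusted, ρ = 0.5 | Adjusted, ρ = 0.7 |
|---|---|---|---|
| 15 v 15 | 26% | 33% | 46% |
| 15 v 21 (loss in Peer Tree only) | 30% | 38% | 52% |

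**6. Gain from baseline adjustment.** The variance of a change score is proportional to 2(1 − ρ), and of a baseline-adjusted score to 1 − ρ². The ratio adjusted/change is (1 + ρ)/2, which is 0.75 at ρ = 0.5 and 0.85 at ρ = 0.7: a reduction of 25% to 15%.

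**The case against.** A reader might infer that the arithmetic is wrong and that 80% power is simply not delivered. The article does not support that. It names an F test and plans a group-by-time analysis, and step 1 shows that a standard interaction calculation returns 42. With the conventional medium f = 0.25 and ρ = 0.5, 42 participants would have 94.6% power. The article never states 0.5 SD; the target came from earlier data that are not shown, and a condensed article need not list every input. All of this stands, and it limits the point to what the sentence means on the scale of the hypothesis.

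The correlation is also unknown. Power for 0.5 SD reaches 74–75% at ρ = 0.8, and setting 1.75/(1 − ρ) equal to the 10.08 of step 1 shows that about ρ = 0.83 would suffice for 80%. So the shortfall depends on the correlation, although it persists across 0.5 to 0.8.

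It is equally tempting to read the 30% threshold as 30% of loneliness scores lost. It is a feasibility criterion built on app log-ins and contact, and controls have no app. The mixed model also keeps partial data. The figures in step 5 are therefore illustrations and probably pessimistic. What remains is that no allowance for any loss is stated.

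Finally, this is a pilot with acceptability, feasibility and safety among its aims. That lowers the stakes, but the objectives still predict a significant difference and the power sentence supports that prediction.

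**Conclusion.** The point holds in a limited form. The figure of 42 is compatible with a valid interaction calculation, but the example that gives it at ρ = 0.5 corresponds to about 0.85 SD between arms, which is not moderate on the scale of the stated hypothesis. For 0.5 SD, power runs from 35% (unadjusted) to 75% (baseline-adjusted, ρ = 0.8) and stays below 80% throughout the range examined. There is no margin for loss, because the number needed and the number recruited are the same.

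This rests on two-sided alpha 0.05, 0.5 SD as the meaning of moderate, equal baselines with a constant later difference, and correlations of 0.5 to 0.8. The attrition figures rest on the further assumption that the app-based threshold turns into missing outcomes.

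**What to change.** - **Restate the power on the between-arm scale.** 42 randomised gives 80% power for about 0.9 SD unadjusted, or about 0.6–0.8 SD adjusted for baseline at correlation 0.7–0.5. For 0.5 SD it gives about 35–60%, up to 75% at correlation 0.8, and less after attrition.
- **Give the assumptions behind 42:** the F test, the effect metric and value, alpha, the correlation and the loss assumed.
- **Adjust for baseline UCLA-LS3.** Within the mixed model, estimate the between-arm loneliness contrasts at post-intervention and at follow-up, each adjusted for baseline. This keeps the follow-up hypothesis and uses a measurement already scheduled.
- **Report the estimate with a 95% confidence interval**, and state that a non-significant result will not be read as absence of effect.

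The cost is rewording and one model specification. No extra participants are needed. The downside is a less favourable stated power.
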